### Skeletal Muscle and Adipose Tissue Mitochondrial Respiratory Function

Measures of mitochondrial respiration were performed in respiration medium (MiR05) at 37°C using high-resolution Oxygraph-2k (Oroboros, Innsbruck, Austria) [71]. All measures were completed in duplicate and carried out in a hyperoxygenated (250-450 nmoL/mL) environment. Skeletal muscle and adipose tissue (abdominal and gluteal subcutaneous adipose tissue) samples were prepared and analyzed according to the methods described [71,72]. Briefly, immediately after tissue collection, samples were stored in ice-cold BIOPS [71] for a maximum of 4 hours before analyses. Skeletal muscle fibers (1-3 mg w/w) and adipose tissue (50-60 mg w/w) were permeabilized in saponin (5 mg/mL BIOPS) for 30 min and 20 min, respectively. Tissue was immediately washed in MiR05 for 2 x 10 min. The multiple substrate-uncoupler-inhibitor titration protocol applied to all tissue is as follows [73,74]:

Medium chain fatty acid oxidation through leak respiration in the absence of adenylates with the addition of malate (2 mM) and octanoly-carnitine (0.2 mM)Maximal flow of electrons through electron transferring flavoprotein and fatty-acid oxidation (ADP 5 mM)Submaximal state 3 respiration capacity specific to complex I (pyruvate 5 mM; glutamate 10 mM)Maximal state 3 respiration, oxidative phosphorylation capacity (Succinate, 10 mM)State 4o respiration, oligomycin-induced leak respiration through inhibition of ATP synthase (Oligomycin 2.5 μM)Electron transports system capacity with the titration of CCCP (0.5 μM titration steps)Inhibition of complex I with the addition of rotenone (0.5 μM)The inhibition of complex III with the addition of antimycin A (2.5 μM)

Complex III inhibition was used for the determination and correction of residual oxygen consumption (nonmitochondrial oxygen consumption in the chamber). Ascorbate (2 mM) and TMPD (0.5 mM) were added to assess cytochrome c oxidase (COX), complex IV activity. TMPD and ascorbate are redox substrates that donate electrons directly to COX, and activity was measured by pmol of O_2_ a minute per mg of wet weight.

Hydrogen peroxide (H_2_ O_2_) flux was measured simultaneously with respirometry in the O2k-Fluorometer (O2k-Fluo LED2-Module Fluorescence-Sensor Green) using the H_2_ O_2_ sensitive probe Amplex UltraRed. Then 10 μM Amplex UltraRed and 1 U/mL horseradish peroxidase (HRP) was added to the chamber. The reaction between Amplex UltraRed and H_2_ O_2_ catalyzed by HRP is fluorescent, similar to resorufin. Calibrations were performed throughout the respirometry experiment to account for degradation of fluorescent over time, with 2 steps of H_2_ O_2_ added at 0.1 μM per step. Mass-specific H_2_ O_2_ were calculated relative to oxygen flux (H_2_ O_2_/O_2_ flux). The H_2_ O_2_/O_2_ flux ratio is frequently applied to evaluate the relative importance of H_2_ O_2_ production at different respiratory states [75].

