### Aims and Objectives

The aim of the study was to identify mechanisms underlying the changes in insulin sensitivity and secretion in response to a 12-week aerobic exercise intervention in obese black SA women.

The objectives of the study were as follows:

to measure changes in insulin sensitivity and secretion (primary outcomes) in response to the 12-week intervention compared with the nonexercise control groupto measure changes in potential primary and secondary determinants (secondary outcomes) of insulin sensitivity and secretionto examine the associations between changes in insulin sensitivity and secretion and changes in the primary and secondary determinants

Primary determinants were as follows:

cardiorespiratory fitnessbody composition and body fat distributionblood pressurelipid profile, including high-density lipoprotein (HDL)- and low-density lipoprotein (LDL)-cholesterol subclasses and HDL functionalityectopic fat deposition (skeletal muscle, liver, and pancreas)skeletal muscle expression of genes and proteins involved in insulin signaling, oxidative capacity, and mitochondrial biogenesisskeletal muscle and serum metabolomics and lipidomic profilegluteal and abdominal subcutaneous adipose tissue expression of genes and proteins involved in inflammation, insulin signaling, oxidative stress, vascularization, adipogenesis, and lipid metabolismcirculating inflammatory cytokine, myokine, and adipokine concentrationsskeletal muscle and adipose tissue mitochondrial respiration and hydrogen peroxide production;gastrointestinal microbiota

Secondary determinants were as follows:

energy expenditure and substrate metabolism at rest and during exercisehabitual physical activity and sedentary behavior patternsdietary intake, red blood cell, and adipose tissue fatty acid compositionsleep quantity and qualitypsychological well-beingperceptions of body image, healthy behaviors, and the exercise intervention

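### Step 3 of the respirometry titration is labelled specific to complex I, but the fatty-acid substrates and ADP of steps 1 and 2 are still present, so it is a combined fatty-acid plus complex I-linked state

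*Protocol article*

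**What the plan says.** All passages are in the protocol article. The section on skeletal muscle and adipose tissue mitochondrial respiratory function gives a single sequence for muscle and both fat depots: "The multiple substrate-uncoupler-inhibitor titration protocol applied to all tissue is as follows". Numbering the listed additions in order, the relevant ones are:

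- Step 1, leak respiration without adenylates, "with the addition of malate (2 mM) and octanoly-carnitine (0.2 mM".
- Step 2, "Maximal flow of electrons through electron transferring flavoprotein and fatty-acid oxidation (ADP 5 mM".
- Step 3, "Submaximal state 3 respiration capacity specific to complex I (pyruvate 5 mM; glutamate 10 mM".
- Step 4, succinate, labelled maximal state 3 respiration.
- Steps 5 and 6, oligomycin, then CCCP (uncoupled state).
- Step 7, "Inhibition of complex I with the addition of rotenone".
- Step 8, antimycin A.

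The only wash described comes after permeabilization and before the titration: "Tissue was immediately washed in MiR05 for 2 x 10 min". The only correction named for the fluxes is this one: "Complex III inhibition was used for the determination and correction of residual oxygen consumption".

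Aims and Objectives lists skeletal muscle and "adipose tissue mitochondrial respiration and hydrogen peroxide production" among the primary determinants, which are secondary outcomes. Changes in these are to be compared between arms by repeated measures ANOVA and correlated with changes in insulin sensitivity and secretion (Proposed Statistics).

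**The concern.** The trial exists to attribute a change in insulin sensitivity to particular mechanisms, so the name given to each respiratory state becomes part of the conclusion. Step 2 is described as fatty-acid oxidation and step 3 as complex I, as if they were two separate readouts. If step 3 still carries the step 2 flux, they overlap. A training effect on fatty-acid oxidation alone could then be described as two findings, one on fat oxidation and one on complex I. The hydrogen peroxide to oxygen flux ratio, which the article says is used to compare respiratory states, would carry the same label at step 3.

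**Working it through.** **Is the fatty-acid input still there at step 3?** The article has no figure to reproduce, so this part is a reading of the sequence.

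1. The assay is a titration with successive additions. Nothing listed between steps 2 and 3 removes octanoylcarnitine or malate or blocks their oxidation.
2. The step 3 label itself presumes carry-over. State 3 is ADP-stimulated respiration, and ADP is listed only at step 2. If ADP remains, so do the substrates added with or before it.
3. Step 2 is described as the maximal fatty-acid-supported flow. That flow is running when pyruvate and glutamate are added.

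Step 3 is therefore fatty-acid plus complex I-linked respiration.

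**How much could this matter?** Let J2 be the step 2 flux, J3 the step 3 flux, d the increment from pyruvate and glutamate, s = J2/J3, and r the relative rise in J2 from training, with no other change. The documents give no fluxes, so s and r are assumptions: s = 0.30 to 0.60, r = 0.20.

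*Full additivity*, J3 = J2 + d:

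- Relative rise in J3 = s × r.
- s = 0.30: 0.30 × 0.20 = 0.06, or 6%.
- s = 0.60: 0.60 × 0.20 = 0.12, or 12%.
- Change in J3 − J2 = 0%.

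*No additivity*, the opposite limit, where J3 is capped and does not move when J2 rises:

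- Relative rise in J3 = 0%.
- J3 − J2 falls by r × J2. Relative to its starting value (1 − s) × J3, the fall is r × s/(1 − s).
- s = 0.30: 0.20 × 0.30/0.70 = 0.086, or about 9%.
- s = 0.60: 0.20 × 0.60/0.40 = 0.30, or 30%.

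So 6-12% is an upper bound for this assumed rise. The increment is clean only under full additivity. If the inputs compete, it errs downward.

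**The case against.** The strongest reply is that the article lists chamber states and defines no analysed complex I variable. Raw step 3 flux, the increment over step 2 and a rotenone-sensitive flux are all left open. The description is explicitly brief, cites methods papers, and may leave flux derivation to them. The brackets evidently show what is newly added, since step 4 is called maximal with only succinate named, so the cumulative design is disclosed. Step 2 is recorded separately, so the data to separate the two exist.

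Most of this stands, and it rules out several stronger readings.

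- A reader might infer that a rise in fat oxidation *is* reported as a complex I effect. The article does not say so. It would follow only if raw step 3 flux were analysed under its printed label.
- A reader might infer that both scores must correlate with insulin sensitivity by construction. Overlap makes steps 2 and 3 correlate with each other. A correlation with insulin sensitivity still needs a real association of at least one component.
- A reader might borrow the GLUT4 effect from the sample size section (0.64/0.69 = 0.93 SD), assume independent additive parts with equal SDs, obtain 0.93/√2 = 0.66 SD at step 3 and 46% power with 20 versus 15 women, and set that against 5% as an error rate. None of those inputs is a respirometry figure, and the 46% is power to detect a true difference in step 3 flux.
- A reader might take rotenone-sensitive flux (step 6 minus step 7) as the clean complex I measure. It is an uncoupled state with all substrates present, and fatty-acid oxidation also feeds complex I.

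The reply does not rescue the label. Calling the state specific to complex I is a positive statement in the article, not a detail left out, and it conflicts with the article's own account of step 2.

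**Conclusion.** The point holds as a mislabelled state with a conditional consequence. Step 3 is combined fatty-acid plus complex I-linked state 3 respiration. If it is analysed as labelled, one mechanism could be read as two. On the assumed 20% rise and 30-60% share, the carry-over into step 3 is at most 6-12%, and less if the inputs are only partly additive. The documents allow no firmer estimate.

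The reach is limited to one mechanistic secondary outcome and the flux ratios labelled by the same states. A correction is still worthwhile, because mechanism attribution is the stated aim and the correction is nearly free.

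**What to change.** 1. Relabel step 3 as combined fatty-acid plus complex I-linked state 3 respiration, for the fluxes and for the hydrogen peroxide ratios.
2. Draw no complex I-specific conclusion from the raw step 3 flux.
3. Report the step 3 minus step 2 increment as the pyruvate/glutamate-linked response, and use it in the arm comparison and in the correlations with insulin sensitivity and secretion. Show steps 2 and 3 beside it, so that a fall in the increment caused by competing inputs can be recognised.
4. Treat any rotenone-sensitive flux (step 6 minus step 7) as supportive only, and say why.

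The cost is a change of name and one subtraction per trace, with no new tissue or assay. The article describes sample and data analysis as still under way, so the change was open when it was written. The downside is that the increment carries the reading error of two states, so it is noisier than the raw flux, and it is free of fatty-acid flux only under full additivity. Both limits should be stated with the results.

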### Fecal Bacterial Community Analysis

Bacterial DNA will be extracted using the ZymoBIOMICS DNA Miniprep kit (Zymo Research Corp., Irvine, USA) according to the manufacturer’s instructions. Bacterial composition will be described by sequencing the V4 hypervariable region of the 16S ribosomal RNA gene. Sequencing libraries will be prepared as per the Illumina MiSeq system instructions (Illumina, San Diego, CA). The pooled library will then be sequenced on the Illumina Miseq sequencing platform (Illumina, San Diego, CA). Raw sequences obtained from the Illumina Miseq will be subjected to a quality check using the FastQC software [76]. Preliminary analysis of the raw data will involve removing primers, barcodes, contaminants, and low-quality bacterial sequences. The 16S pair-end reads will be assembled by joining forward and reverse of demultiplexed sequence reads. The output file will then be processed for quality filtering. Chimeric sequences will be filtered by UCHIME algorithm in USEARCH platform. We will use QIIME [77] to cluster sequences into operational taxonomic units (OTUs) based on a sequence similarity threshold of 97%. The SILVA database will be used to assign taxonomic identities to the OTUs. Moreover, we will use the PICRUSt (Phylogenetic Investigation of Communities by Reconstruction of Unobserved States) and BugBase softwares to predict the metabolic function [78,79]. Raw data in fastq format will be made available in a public sequence database.

### Statistics

#### Sample Size Determination

Sample size determination was based on our primary outcome using the study of Nordby et al [80], with a significance level of *P*<.05 and power of 80%. On the basis of the change in normalized glucose clearance (measured using a euglycemic hyperinsulinemic clamp) from pre- to postintervention (12-week aerobic training) compared with the nontrained control group (8.2 [SD 5.9] vs −1.8 [SD 6.2] mL/kg/min FFM/nmoL/L insulin, respectively), 6 participants per group would be required to detect a significant difference between groups. These numbers correspond to those of Ortega et al [81] who compared glucose tolerance tests to detect the insulin sensitizing effects of a bout of continuous exercise and reported that 6 participants would be required to detect a change in insulin sensitivity when using a FSIGT. In order to account for the secondary outcomes, using changes in skeletal muscle glucose transporter (GLUT)4 in response to a 12-week training program as the proxy (0.65 [SD 0.69] vs 0.01 [SD 0.69] AU for training vs control group), 18 women would be required to detect a difference between groups [81]. On the basis of these calculations, and a dropout rate of 10% (2/20), 20 participants per group were selected.

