## Results

### Participant Enrollment, Allocation, Follow-Up, and Analyses

Information on participant enrollment, allocation, follow-up, and analysis is shown in Figure 2. Standards of reporting were based on the CONSORT 2010 checklist for randomized control trials. A total of 45 participants were enrolled in the study and randomized into exercise (n=23) and control (n=22) groups. Of these, 10 participants did not complete the intervention (dropout; n=3 exercise, n=7 control) resulting in a final sample of 20 exercise and 15 control participants.

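### Minor: by the planned two-sided comparison, 6 per group (primary) and 18 per group (GLUT4 proxy) give 73% and 77% power, not the stated 80%; the primary outcome stays well powered in the final sample

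*Protocol article*

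**What the plan says.** All planning figures are in the Sample Size Determination section of the protocol article. The calculation is made "with a significance level of *P*<.05 and power of 80" percent; whether the test is one- or two-sided is not stated.

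- **Primary outcome.** The assumed change in glucose clearance, trained versus control, is "8.2 [SD 5.9] vs −1.8 [SD 6.2] mL/kg/min FFM/nmoL/L insulin". From this, "6 participants per group would be required to detect a significant difference between groups". A second study, of a single bout of exercise, is cited as also arriving at 6.
- **Secondary proxy.** The assumed change in muscle GLUT4 is "0.65 [SD 0.69] vs 0.01 [SD 0.69] AU for training vs control group", and "18 women would be required to detect a difference between groups".
- **Final size.** On the basis of these calculations and "a dropout rate of 10% (2/20), 20 participants per group were selected".

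The Proposed Statistics section plans a repeated measures ANOVA to compare change between the two groups. The Results section on enrollment and follow-up reports 45 randomized (23 exercise, 22 control) and 10 dropouts (3 and 7), "resulting in a final sample of 20 exercise and 15 control participants". The Discussion calls the sample size limited, says the study is powered for its main outcome measures, and allows that secondary data may serve as pilot data.

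**The concern.** A sample size formula built on normal quantiles ignores that the SD is estimated. At 6 per group the t test has only 10 degrees of freedom, and the approximation is then poor. The GLUT4 figure has a second, smaller fault: the formula gives just over 18, and a required number is rounded up, not down.

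The GLUT4 calculation matters more, because it, and not the primary outcome, produced 20 per group. The purpose of the study is mechanistic, so results on secondary outcomes such as GLUT4 will be read closely. A reader who takes 80% at face value may put slightly too much weight on a null result for an effect of that size.

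**Working it through.** **Inputs**, all from Sample Size Determination except the final sample (Results):
- alpha .05, two-sided assumed; target power 80%
- primary: difference 8.2 − (−1.8) = 10.0; SDs 5.9 and 6.2
- GLUT4: difference 0.65 − 0.01 = 0.64; SD 0.69
- the SDs are taken as SDs of change, as the text presents them
- final sample 20 versus 15

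**Test.** With one pre and one post measurement, the group-by-time comparison in a repeated measures ANOVA is the same as a two-sample t test on change.

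**Step 1: standardised effects.**
- Primary: pooled SD = √((5.9² + 6.2²)/2) = 6.05; d = 10.0/6.05 = 1.652
- GLUT4: d = 0.64/0.69 = 0.928

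**Step 2: reproduce the article's figures (normal approximation).** n per group = 2(1.96 + 0.842)²/d².
- Primary: 5.75, so 6. Normal-formula power at 6 is 81.6%.
- GLUT4: 18.25, stated as 18; rounded up it is 19. Normal-formula power at 18 is 79.5%.
- Dropout: 18/0.9 = 20 per group. This also shows that 18 is a per-group figure.

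The stated numbers therefore come from this formula, with 18.25 rounded down.

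**Step 3: power of the planned test.** Noncentral t, df = n₁ + n₂ − 2, noncentrality = d/√(1/n₁ + 1/n₂).

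| Outcome | n per group | df | Noncentrality | Power |
|---|---|---|---|---|
| Primary | 6 | 10 | 2.86 | 73.2% |
| Primary | 7 | 12 | 3.09 | 81.0% |
| GLUT4 | 18 | 34 | 2.78 | 77.1% |
| GLUT4 | 19 | 36 | 2.86 | 79.4% |
| GLUT4 | 20 | 38 | 2.93 | 82% |

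So 7 and 20 per group are needed. With 10% dropout the GLUT4 figure becomes 20/0.9 = 22.2, so 23 per group. Under the plan as written (20 enrolled, 10% lost, 18 left), GLUT4 power is 77.1%.

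**Step 4: final sample, 20 versus 15 (df 33).**
- Primary: 99.7%
- GLUT4: 75.0% (normal formula 77.5%)
- Effect detectable with 80% power: d = 0.99

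**Step 5: dropout.** 10/45 = 22% overall; 7/22 = 32% in control and 3/23 = 13% in exercise, against 10% allowed.

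**Step 6: sensitivity to sidedness.** With a one-sided .05 t test, power is 84.5% at 6 per group, 86.0% for GLUT4 at 18 per group, and 84.5% for GLUT4 at 20 versus 15. The one-sided normal formula gives 5 and 15, and the one-sided t test needs 6 and 16. Neither yields the stated pair of 6 and 18, so the two-sided reading fits the article better.

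**The case against.** The best defence is that 6 and 18 follow from the article's own inputs by a standard formula, that the exact sizes differ by only 1 and 2 participants, and that nobody planned to run the trial with 6 per group. Much of this stands: the matter is a choice of formula plus one rounding, not a gross miscalculation, and the 6 has no practical consequence. What remains is that 80% is not delivered by the planned two-sided test at either size, and that 18 misses it slightly (79.5%) even by the lenient formula.

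Enrolment of 23 and 22 also came close to the corrected 23 per group; at those numbers GLUT4 power is 86% before losses. The gap in the final sample is therefore largely a matter of dropout, which the article reports openly. An exceeded dropout allowance is not an error in the plan.

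Four stronger readings are tempting, and the article does not support them:
- *The primary outcome is underpowered.* It has 99.7% power at 20 versus 15 under the assumed effect.
- *The GLUT4 figure of 18 is a total.* At 9 per group power would be 46%, but 18/0.9 = 20 per group rules this out. Only the words are missing.
- *The GLUT4 citation is wrong.* Reference 81 is described as a comparison of glucose tolerance tests after one exercise bout, yet is also cited for GLUT4 change over 12 weeks of training. That is a reason to check; an error cannot be shown without the source.
- *The article promises 80% power for secondary outcomes in general.* It uses GLUT4 as one proxy, and the Discussion claims power only for the main outcome measures.

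**Conclusion.** The sample size statement is wrong as written, but the point is minor. Assuming a two-sided .05 t test on change and the article's effects and SDs, the stated sizes give 73% (primary, 6 per group) and 77% (GLUT4, 18 per group) in place of 80%. The shortfalls are about 7 and 3 percentage points; the sizes needed are 7 and 20 per group. The first has no effect on the trial. The second bears on the calculation that set 20 per group. In the final sample GLUT4 power is 75%, or 77.5% by the normal formula, so it is below 80% either way; part of that is realised dropout. A one-sided test would remove the shortfall, but the article does not state one and its two figures do not fit one.

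**What to change.** In Sample Size Determination:
- State that the test is two-sided, if that is what was intended.
- Give the required sizes as 7 per group (primary) and 20 per group (GLUT4), or 23 per group for GLUT4 with 10% dropout, and mark the GLUT4 figure as per group.
- Add that the final 20 versus 15 gives 75% power for the assumed GLUT4 effect and 80% power for about 0.99 SD, while the primary outcome keeps 99.7% power under its assumed effect.
- Check whether reference 81 is the intended source of the GLUT4 values.

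The cost is a few sentences and a slightly less favourable power figure for the secondary proxy. No analysis changes and no further enrolment is needed.

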#### Proposed Statistics

Results will be presented as means (SD), or medians and interquartile ranges for non-normally distributed data. Data will be normalized by log transformation if required. Repeated measures ANOVA will be used to compare differences in the change of outcome variables between the control and exercise groups in response to the exercise/control intervention. Pearson and/or Spearman correlations will be used to examine associations between changes in primary and secondary outcome variables. Data will be analyzed using StataSE (version 14, StatCorp, Texas, USA) and IBM SPSS Statistics 24 (Version 24.0, Armonk, NY, USA).

Comprehensive metabolite profiling data will be evaluated via a combination of multivariate analysis methods and univariate statistics, that is, Principal Component Analysis (PCA), Orthogonal Partial Least Squares (OPLS), and its extensions [64]. In addition, we will perform an extensive validation to determine the model significances, using both internal, ANOVA on the cross-validated model patterns, and external validation, independent sample prediction. Model scores (subject level) will be used to visualize and interpret the differences in metabolic response between predefined patient groups or subgroups, or of individual patients responding differently to the interventions. Model loadings (variable level) combined with univariate *P* values will be used as the base for mechanistic interpretation and to highlight significant metabolites or metabolite patterns.

For bacterial community analysis, basic statistical tests will be performed using QIIME [77] and R software will be used for advanced statistical analysis. Beta-diversity will be evaluated by calculation of weighted and unweighted Unifrac distances. The Shannon and Simpson diversity indices will be employed to study alpha-diversity. The relationship between the composition of the fecal bacteria and exposure variables will be determined using weighted generalized ridge regression methods [82] and the lasso [83]. We will use Dirichlet multinomial models or ecological approaches such as multi-species occupancy models to evaluate interactions and shift in fecal bacterial communities over time [84,85].

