## Methods

### Study Design

In this randomized controlled research study, 45 obese sedentary black SA women were block (2-4 participants) randomized (Microsoft Office, Excel, 2013) into control or experimental (exercise) groups (Figure 1). Block randomization was performed by the project manager after participants completed preintervention testing to ensure that investigators performing the testing were blinded to group allocation. The exercise group completed 12 weeks of supervised combined aerobic and resistance training (40-60 min, 4 days/week) but maintained their usual dietary behaviors. The control group were instructed to continue their habitual physical activity and dietary behaviors and to refrain from initiating any exercise programs. Before and following the 12-week intervention period (exercise or control), insulin sensitivity and secretion (primary outcome), as well as the proposed determinants of insulin sensitivity and secretion (secondary outcomes) were measured. In addition, dietary intake, sleep quality and quantity, physical activity, and sedentary behavior were monitored for a minimum of 4 days every 4 weeks.

This study was approved by the Human Research Ethics Committee at the University of Cape Town (HREC REF:054/2015). The study was performed in accordance with the principles of the Declaration of Helsinki (1964, amended last in Fortaleza Brazil, 2013), ICH Good Clinical Practice (GCP), and the laws of SA. Participants provided written informed consent before participation in the screening and the research study. Participant recruitment and testing procedures occurred over an 18-month period, between July 2015 and December 2016. Sample and data analysis began in January 2017 and are currently ongoing.

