### Monthly Monitoring

#### Physical Activity, Sedentary Behavior, and Sleep

Physical activity and sleep quality and quantity were measured using accelerometry (ActiGraph GTX3+, ActiGraph LLC, Pensacola, Florida), and sedentary behavior was measured using activPAL (activPAL3c, PAL Technologies Ltd, Glasgow, UK) at preintervention, week 4, week 8, and postintervention. The ActiGraph was initialized to record data in 60-second epochs and was set to measure motion in all 3 axes, with the inclinometer function activated. The ActiGraph was worn on the right hip with a lightweight belt, and participants were instructed to wear it for 24 hours a day over a 7-day period, except when swimming, bathing, and showering. Participants were instructed to complete a sleep diary to capture awake and sleep times. Physical activity and sleep data were captured and analyzed using the ActiLife Software Version 6 (ActiLife software; Pensacola, FL, USA). A minimum of 4 days of wear time, with 600 min per day of wake time was required for data analysis. The 4 days of wear needed to be inclusive of 3 weekdays and 1 weekend day. For the exercise group, at least one of the weekdays needed to be an “exercise day.” Nonwear time was defined as 60 continuous minutes of no counts (zeros) [54]. Vector magnitude cut-points were used for analysis [55,56]. The vector magnitude represents the summed value of all 3 axes measured from the ActiGraph, calculated as the square root of the total sum of each axis, squared (X^2^+Y^2^+Z^2^), then square rooted [57]. Counts/minute between 200 and 2689 represents light intensity physical activity, 2690 to 6166 represents moderate intensity physical activity, 6167 to 9642 represents hard intensity physical activity, and >9643 counts per minute represents very hard intensity physical activity. Data were analyzed for any physical activity occurring in 1-min and 10-min bouts/intervals. Within each 10-min bout, 1- or 2-min of “dropped” counts were allowed, thereby excluding bouts of activity where a drop-in count is greater than 2 min (within the 10-min period) occurred. Sleep data were analyzed for sleep latency, total sleep time, wake after sleep onset, and sleep efficiency. Participants completed a sleep diary that was used to mark wake and sleep hours, which was further verified based on movement measured by the activPAL.

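### For outcomes measured only before and after training, the planned group-by-time ANOVA is a change-score t test: valid, but usually less precise than adjusting for the baseline value already collected

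*Protocol article*

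**What the plan says.** The general analysis is fixed under Proposed Statistics: "Repeated measures ANOVA will be used to compare differences in the change of outcome variables between the control and exercise groups". No baseline covariate is named. Separate methods are given for the muscle gene array (paired t tests with false discovery rates, in the section on gene and protein expression), for metabolite profiling (PCA and OPLS) and for the fecal bacteria (diversity measures, ridge regression, lasso and Dirichlet multinomial models).

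The primary outcomes have two time points. Study Design reads: "Before and following the 12-week intervention period (exercise or control), insulin sensitivity and secretion (primary outcome" and so on. Activity, sedentary behavior and sleep have four: "at preintervention, week 4, week 8, and postintervention". Diet is recorded at the same four times.

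The baseline value precedes allocation: "Block randomization was performed by the project manager after participants completed preintervention testing". Ten women dropped out, "resulting in a final sample of 20 exercise and 15 control participants".

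Sample Size Determination works on change scores, "with a significance level of *P*<.05 and power of 80" percent. The primary planning effect is "8.2 [SD 5.9] vs −1.8 [SD 6.2] mL/kg/min FFM/nmoL/L insulin, respectively", from which "6 participants per group would be required to detect a significant difference between groups". A secondary proxy, change in muscle GLUT4 (0.65 versus 0.01, SD 0.69 in each arm), gives 18, read here as per group, and 20 per group after 10% dropout.

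**The concern.** A change score subtracts the whole baseline value. When pre and post values correlate only moderately, that subtracts too much and adds baseline noise to the contrast. Regressing the post value on baseline removes only the part of baseline that predicts the outcome. Because baseline was measured before allocation, it is a legitimate covariate and already paid for.

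The same fact can be seen for a single trial. If the arms differ at baseline by chance, regression to the mean shifts the change contrast away from the true effect, and nothing in the planned test corrects this. With 15 and 20 women such differences can be appreciable.

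At stake is precision on two-time-point outcomes in a trial whose control arm has ended at 15, fewer than the 18 used for the GLUT4 proxy.

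**Working it through.** **1. The plan's own figures** (two-sided 5% assumed, 80% power, normal approximation).
- Primary: difference 8.2 − (−1.8) = 10.0; pooled SD = √[(5.9² + 6.2²)/2] = 6.05; n = 2 × [6.05 × (1.960 + 0.842)/10]² = 5.75, so 6 per group. The exact t calculation gives 6.86, so 7.
- GLUT4: difference 0.64, SD 0.69; n = 2 × [0.69 × 2.802/0.64]² = 18.25 per group (exact t: 19.3). The plan states 18.
- Dropout: 18/0.9 = 20.

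The stated sizes are reproduced closely enough.

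**2. The identity.** With one pre and one post value, the group-by-time F equals the squared two-sample t on change scores. In a simulated data set of 15 and 20, both routes gave 3.7897. The identity does not carry over to outcomes with four time points.

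**3. Relative precision.** Let s be the common pre and post SD and r the pre-post correlation.
- Change score: residual variance 2s²(1 − r).
- Baseline-adjusted: s²(1 − r²).
- Ratio: 2/(1 + r), so the equivalent number of women is 35 × 2/(1 + r).
- Estimating the slope costs a factor of 1 + 1/(35 − 4) = 32/31.

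The documents give SDs of change but no cross-sectional SD or correlation for the outcomes, so r is an assumption:

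| r (assumed) | Large-sample equivalent N | After slope penalty | Simulation, 20,000 trials of 15 vs 20 |
|---|---|---|---|
| 0.3 | 53.8 | 52.2 | 52.1 |
| 0.5 | 46.7 | 45.2 | 44.8 |
| 0.7 | 41.2 | 39.9 | 39.5 |
| 0.8 | 38.9 | 37.7 | not run |
| 0.9 | 36.8 | 35.7 | 35.8 |

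Break-even is at 2/(1 + r) = 32/31, that is r = 0.94. At r = 1 the equivalent N is 35 × 31/32 = 33.9, so with equal SDs the most that can be lost is about one woman's worth of precision.

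**4. Unequal SDs.** If the post SD is k times the pre SD, the large-sample equivalent is 35(1 + k² − 2rk)/[k²(1 − r²)]. For r = 0.3, 0.5 and 0.7 this gives 69.7, 61.2 and 55.8 at k = 0.8, and 44.6, 39.2 and 35.7 at k = 1.25.

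**5. Power at 20 versus 15** (exact t).
- Primary planning effect by change score: 99.7%.
- GLUT4 effect by change score: 75%.
- GLUT4 effect with baseline adjustment (slope penalty, 32 df): 80% at r = 0.7, 85% at r = 0.5, 90% at r = 0.3.

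**6. Chance imbalance.** The SE of a baseline mean difference is √(1/15 + 1/20) = 0.34 SD. Given a baseline difference d and equal SDs, the post difference is expected to be the effect plus rd, so the change contrast is the effect minus (1 − r)d. A one-SE imbalance at r = 0.5 shifts it by 0.5 × 0.34 = 0.17 SD. This is the loss of step 3 seen within one trial, not a further loss.

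**The case against.** The planned comparison is not wrong. It is unbiased under randomisation, it matches the stated objective of measuring changes, and it matches a sample size built on change scores. A condensed article may also leave covariates to an analysis plan that is not shown. All of this stands; if that plan already names the baseline value as a covariate, the point is met. What remains is that the one method the article states is a comparison of change, and a more precise alternative costs almost nothing.

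A reader might infer more than the documents support:

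- **That 35 women certainly yield the precision of 41 to 54.** That range needs r between 0.3 and 0.7, equal SDs and large-sample formulas. The documents give neither r nor the SD ratio, and at 35 women the range is nearer 40 to 52.
- **That every outcome gains.** The gene array, metabolomics and microbiota have their own stated methods, and diet, activity and sleep have four time points. Very stable measures may gain nothing. For weight, with a baseline SD of about 10 kg (Table 3 gives 8.7 to 12.0) and an assumed SD of change of 2 to 3 kg, r = 1 − SD²/(2 × 10²) is 0.98 to 0.96, past break-even.
- **That the primary outcome is underpowered.** The 18 belongs to the GLUT4 proxy; the primary requirement is 6 per group, and 15 exceeds it. The limit on this reassurance is that the primary planning effect comes from a clamp measure, whereas this trial uses the FSIGT, and no planning effect is given for insulin secretion.
- **That the arms are imbalanced on the primary outcomes.** Baseline insulin sensitivity and secretion are not reported, so imbalance is possible but not shown.

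**Conclusion.** The point holds as an avoidable loss of efficiency, with exposure to chance baseline imbalance, for univariate outcomes measured only before and after 12 weeks, both primary outcomes included. It is not an invalid analysis. If r is 0.3 to 0.7 and pre and post SDs are similar, adjustment is worth about 5 to 17 extra women on a base of 35; the gain is close to nil from r of about 0.9. The practical benefit is clearest for secondary outcomes of the GLUT4 kind, where adjustment would bring power back to or above the planned 80%. That figure reads 0.69 as an SD of change and 18 as per group. At its own planning effect the primary comparison has little to gain in power, although its confidence interval would still usually narrow. Adjustment does nothing about the unequal dropout itself (7 of 22 controls, 3 of 23 exercisers), which is a separate matter.

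**What to change.** For insulin sensitivity, insulin secretion and the other univariate outcomes with two time points, replace the comparison of change by a linear model of the post value on arm with the baseline value as covariate, on the log scale where the outcome is skewed. A mixed model with a common baseline mean for both arms is the equivalent alternative, and can also keep the baseline values of women who dropped out. Report the adjusted arm difference with its 95% CI. Leave the stated methods for the gene array, metabolomics and microbiota as they are.

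The cost is one degree of freedom and a documented amendment. The article says testing ended in December 2016 and that analysis began in January 2017 and was continuing, so the change should be dated, justified and recorded before arm-level results are examined. If any have been seen already, the record should say so; otherwise the change could be taken for a post hoc switch.
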